### Patient recruitment

Recruitment will be conducted from April to July 2023. Patients who are scheduled for chemotherapy will be assessed by the nurse on duty, who will review their latest laboratory results, medical records, vital signs and ECG results, to determine whether they are eligible to undergo chemotherapy. The patients who pass the screening process will be asked whether they are willing to be involved in the study and will be asked to sign the informed consent form. Patients who are willing and who sign the informed consent form will be given a sealed envelope containing a random number indicating their group allocation. The participants will be evaluated (pretest) by the outcome assessor (research nurse) before they enter the chemotherapy room. After the evaluation, the researcher will open each participant’s envelope and see the random number that they have been assigned (without the knowledge of the participants or the outcome assessor). If the number assigned is between 1 and 40, the participant will be directed to the chemotherapy room on the east side of the hospital (intervention group); if the number is between 41 and 80, the participant will be directed to the chemotherapy room on the west side of the hospital (control group). We will for the participants in the intervention and control groups to be directed to different chemotherapy rooms, and a research assistant (RA) will accompany the participants to the rooms to minimise contamination of information between participants, between participants and intervention providers and between the nurses or doctors on duty.^42^

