## Introduction

The cancer incidence in Indonesia (136.2/100 000 population) is the 8th highest in Southeast Asia and 23rd highest in Asia.^1^ According to Basic Health Surveillance (Riskesdas),^2^ the prevalence of cancer in Indonesia increased from 1.4 in 2013 to 1.49 in 2018. Of the total of 396 914 cancer cases in Indonesia in 2020, the top three most common cancer types were breast cancer (65 858 cases; 16.6%), cervical cancer (36 633 cases; 9.2%) and lung cancer (21 392 cases; 8.8%).^3^ The region with the highest prevalence of cancer is the Special Region of Yogyakarta (DIY) Province (4.86/1000 population), and 23% of the patients with cancer in this region receive chemotherapy, which is the second-most-common cancer management strategy after surgery.^2^

Patients undergoing chemotherapy experience various adverse effects.^4^ Moreover, they may experience physical and psychological discomfort caused by the treatment drugs, invasive procedures and chemotherapy environments. In general, 86% of patients with cancer experience pain, nausea, vomiting, mucositis, diarrhoea and alopecia.^5 6^ Other side effects include psychological problems, such as anxiety, feelings of hopelessness, depression, anger, fear, vulnerability and a sense of loss of control.^7^ Management of the side effects of chemotherapy by using drugs is not fully effective and may cause other side effects, which can cause further patient discomfort.^8 9^

Comfort is defined as a lack of pain, distress, worry and uneasiness, and it is one of the most crucial factors in holistic nursing care.^10 11^ Focusing on patients’ biophysiological aspects (eg, symptom management) as well as psychospiritual, environmental and sociocultural aspects related to healing is crucial for maintaining their well-being.^12^ Kolcaba explained that in addition to providing basic care to patients, nurses must provide special and unique nursing care to each patient to increase patient comfort.^13 14^ Patients with cancer require physical, social and spiritual support and a comfortable environment to have a sense of life meaning.^12 15 16^ Meeting the comfort needs of patients with cancer positively affects the patients’ satisfaction with the services they receive, their treatment adherence and their overall quality of life.^11 17^

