### Sample size calculation

The sample size was calculated using free-to use software, namely G*Power for Windows V.3.1.9.6.^33^ The effect size is 0.81, type 1 error (α)=5% (two-tailed), power (1−β) 90% and the allocation ratio between the groups is 1:1. The effect size was set with reference to previous studies with similar outcomes.^9^ According to the G*Power calculation, the study sample size should be 34 per group. With consideration of an expected dropout rate of 15%, the sample size was increased to 40 per group.

The participant dropout criteria are as follows:

The patient being unwilling to continue the sequence of the study process (lost to follow-up).The patients experiencing drug extravasation incidents or severe side effects during chemotherapy.

The consecutive sampling technique will be applied. This non-probability sampling method involves recruiting all individuals from the accessible population during a given time interval or for a specific sample size. Patients with cancer who have scheduled chemotherapy and meet the requirements of the data collection time will be asked to participate in the study.

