Anxiety is measured using the Visual Analogue Scale for Anxiety (VAS-A) in the form of a horizontal line with a scale of 100 mm or 10 cm, with the left by the words ‘not at all anxious’ and on the right by ‘extremely anxious’.^36 37^ VAS-A has a sensitivity of 76.8%, specifications of 64.9% and internal reliability consistency (Cronbach’s α ≥0.7).^36 37^

Pain is measured using the Numerical Rating Scale (NRS). The NRS consists of numerical scale; from 0 to 100 (101-point scale), 0 to 10 (11-point scale) or 1 to 10 (10-point scale). This study will use a 0–10 NRS due to it provides more sufficient sensitivity to measure pain in most patients with cancer.^38^ The NRS has been declared valid and reliable for subjective measurement of cancer pain, both due to adverse effects of cytotoxic agents, cancer treatment procedures (surgery, radiotherapy and chemotherapy) and the malignancy of the cancer itself.^39^

Pulse rate and blood pressure (systolic and diastolic pressure) are measured using an automatic digital sphygmomanometer. According to American Heart Association, the regular resting heart rate for adults is 60–100 beats per minute, and systolic blood pressure is above 90 mm Hg and less than 120 mm Hg, with a diastolic pressure between 60 mm Hg and less than 80 mm Hg.^40^

Comfort and self-efficacy for symptom management will be measured at two time points: at baseline (before chemotherapy premedication) and post-test (after the chemotherapy session is completed). Anxiety, pain and vital signs (pulse rate and blood pressure) will be measured at five time points: thrice at pretest (baseline data collection, before the installation of intravenous access and before administration of VR intervention) and twice at post-test (immediately after intervention and after the chemotherapy session is completed). The timeline of the data collection and measurement is presented in table 2.

**Table 2 T2:** Timeline of data collection and measurements

Assessment/measurement instrument	Study period				
	T0	T1	T2	T3	T4
Demographic variables	**X**				
Clinical characteristics	**X**				
SGCQ	**X**				**X**
SE-CSSMS	**X**				**X**
VAS-A	**X**	**X**	**X**	**X**	**X**
NPRS	**X**	**X**	**X**	**X**	**X**
Blood pressure	**X**	**X**	**X**	**X**	**X**
Pulse rate	**X**	**X**	**X**	**X**	**X**

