### Data analysis

The collected data will be processed using IBM SPSS statistical software V.23 for Windows through editing, coding and data entry processes. The statistician will be blinded to the study outcomes and will conduct analyses on the basis of the labelling of the groups. For the treatment group, the demographic and clinical variables recorded at enrolment will be tabulated. The descriptive statistics will be presented as numbers, means, SDs, medians, minimums and maximums. Homogeneity and normality tests will be conducted before the bivariate analysis test. A homogeneity test for categorical data (age, sex, education level, marital status, occupation, income, the presence of a family member or caregiver during chemotherapy, type of cancer, stage of cancer, duration of cancer diagnosis, chemotherapy cycle and ECOG Scores) will be performed using the χ^2^ test or Fisher’s test, whereas a homogeneity test for numerical data (height and weight) will be performed using Levene’s test if the data are normally distributed and using the Mann-Whitney U test if the data are not normally distributed. Both groups will be considered to be homogeneous if p>0.05. Bivariate analysis will be used to determine the differences in the mean scores for comfort level and symptom management self-efficacy before and after treatment in the intervention and control groups. If the data distribution is normal, we will use a paired t-test and independent t-test. However, if the data distribution is not normal, the non-parametric Wilcoxon and Mann-Whitney U tests will be used if significant differences are identified (p<0.05). For anxiety, pain and vital-sign (blood pressure and pulse rate) outcome measurement analysis, General Linear Model-Repeated Measure (GLM-RM) statistics will be used. The GLM-RM is a statistical test used for the comparative analysis of two unpaired numerical data groups with more than two measurements and is applied when the effect of a treatment or intervention is measured at different time points. If the data are not normally distributed, the repeated Mann-Whitney alternative test with Bonferroni correction will be used. The present study will use statistical method to adjust for potentially confounding effects of the S-VR intervention on the patient’s outcomes. These confounders include age, gender, education, cancer stage, chemotherapy cycle, assistance during chemotherapy and comorbidities. Multivariate model can handle identified confounders and minimise the bias effect of the intervention.^45^ Linear regression analysis will be applied by using the enter method. Adjustment by using this analysis can clarify that how much the confounders in the model distort the intervention and outcome.^46^

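### Each arm is tied to its own chemotherapy room, so for comfort and self-efficacy the S-VR effect cannot be separated from a difference between rooms or their staff.

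*Protocol article*

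**What the plan says.** The protocol article, Patient recruitment, allocates by the number in the envelope. For numbers 1 to 40, "the participant will be directed to the chemotherapy room on the east side of the hospital (intervention group"). For numbers 41 to 80, "the participant will be directed to the chemotherapy room on the west side of the hospital (control group"). No rotation, shared use or exception is described. The reason given for separate rooms, with a research assistant accompanying participants, is "to minimise contamination of information between participants, between participants and intervention providers and between the nurses or doctors on duty".

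The same section fixes when the baseline is taken: "The participants will be evaluated (pretest) by the outcome assessor (research nurse) before they enter the chemotherapy room". Under Outcomes, comfort and symptom-management self-efficacy are measured twice, "at baseline (before chemotherapy premedication) and post-test (after the chemotherapy session is completed"). Anxiety, pain, pulse and blood pressure are measured at five points. T2 falls just before the intervention and T3 immediately after it (table 2 and its footnote).

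The Introduction says of patients having chemotherapy that "they may experience physical and psychological discomfort caused by the treatment drugs, invasive procedures and chemotherapy environments". It also counts environmental aspects among those that matter for patients' well-being.

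The Data analysis section gives the adjustment set: "These confounders include age, gender, education, cancer stage, chemotherapy cycle, assistance during chemotherapy and comorbidities". Neither that section nor the list of strengths and limitations mentions room.

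**The concern.** Randomisation balances patients between the arms. It does not balance rooms, because the room is assigned together with the arm. Whatever differs between the east and west rooms, including the staff on duty in them, therefore differs between S-VR and control for the whole trial.

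This matters more than usual because the primary outcome is comfort, and the protocol itself lists the treatment environment as a source of discomfort. The intervention lasts about 10 minutes, whereas the room acts throughout the session. A difference in comfort at the end of the session could come from S-VR, from the room or from both. A room difference in the opposite direction could hide a real benefit.

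**Working it through.** **1. The plan's own figure.** Inputs from Sample size calculation: d = 0.81, two-sided α = 0.05, power 90%, 1:1 allocation. For a two-sample t-test with n per arm, the noncentrality is d·√(n/2) on 2n − 2 degrees of freedom. Power is 0.8998 at n = 33 and 0.908 at n = 34, so 34 per group is reproduced. Allowing for 15% dropout, 34 / 0.85 = 40 per group, as stated. The sample size is not at issue here.

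**2. Identifiability.** Code arm as 1 for S-VR and 0 for control, and room as 1 for east and 0 for west. Under the allocation rule the two columns are identical for all 80 participants. The design matrix with intercept, arm and room has rank 2 of 3, and this holds at any sample size. Adding room to the regression therefore cannot help.

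**3. Does baseline help?** It depends on where the earlier reading is taken.

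| Outcome | Readings | Can a stable room shift cancel? |
|---|---|---|
| Comfort, self-efficacy | T0 (before room entry), T4 | No: the whole room exposure lies between the two readings |
| Anxiety, pain, pulse, blood pressure | T0 to T4 | Largely, in the T2-to-T3 change, if T2 is taken in the room; not in contrasts with T0 or at T4 |

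The article does not say where T2 is taken. It follows the point before intravenous access and premedication (T1), and the intervention is given during chemotherapy, so the treatment room is likely.

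**4. Possible size for comfort.** The documents give no room difference, so the shift r (in SD units of the analysed score) is an assumption and is shown as a range. With no S-VR effect, the noncentrality is r·√(n/2). For example, at r = 0.3 and n = 40 it is 0.3 × √20 = 1.34. The probability that a two-sided 5% t-test rejects is:

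| Assumed room shift r | 34 per arm | 40 per arm |
|---|---|---|
| 0.1 SD | 6.9% | 7.3% |
| 0.2 SD | 12.8% | 14.3% |
| 0.3 SD | 23.0% | 26.3% |
| 0.5 SD | 52.9% | 59.8% |

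The nominal rate is 5%. For scale, 0.5 SD is 0.5 / 0.81 = 62% of the planned effect.

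**5. What balancing the rooms does.** With 20 per arm in each room the matrix has rank 3 of 3. The variance of the arm effect, adjusted for room, is 2/40 = 0.05 SD², the same as without room. N need not change.

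**6. What a late, partial swap does.** Suppose only the last k of 40 per arm change rooms. The arm–room correlation is ρ = 1 − 2k/40, and the variance of the adjusted arm effect is inflated by 1/(1 − ρ²).
- k = 4: ρ = 0.8 and inflation is 1/0.36 = 2.78. Effective N is 80 / 2.78 ≈ 29, and power at d = 0.81 falls from about 95% to about 57%.
- k = 8: ρ = 0.6 and inflation is 1/0.64 = 1.56. Effective N is about 51 and power about 82%.

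**The case against.** **Contamination control is a deliberate reason for separate rooms.** This stands as a reason to keep the arms apart. It does not require one permanent room per arm. Swapping rooms by calendar still separates participants on any given day, but it gives up part of the protection among duty staff, who would see both interventions in different weeks.

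**No difference between the rooms is shown.** This also stands. Both rooms appear to belong to one chemotherapy unit, and both arms receive standard care. A reader might infer that the trial's result will be a room effect, or that the false-positive rate is some particular figure. The documents support neither. The percentages above are conditional on assumed shifts, and at 0.1 SD the rejection rate is close to nominal. What remains is that the design can neither detect nor exclude a room difference in comfort, and the article does not say that the rooms or their staffing are comparable.

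**Some outcomes have a reading just before the intervention.** A reader might infer that every outcome carries the full room difference. That goes too far for anxiety, pain and vital signs, where the T2-to-T3 change would remove most of a stable shift if T2 is taken in the room. It would not remove a room effect that changes over that interval.

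**A swap may come too late.** Recruitment was planned for April to July 2023 and the article is dated 25 July 2023. The objection holds if few participants remain, as step 6 of the working shows, so the fix needs a second branch.

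**Conclusion.** The point holds for comfort, the primary outcome, and for self-efficacy. The confounding of S-VR with room is complete, follows from the stated allocation rule and the T0/T4 timing, and cannot be repaired in the analysis. For anxiety, pain and vital signs it holds for contrasts with T0 and at T4. It is much weaker for the T2-to-T3 change, provided T2 is taken in the room.

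The size and direction of any actual bias are unknown. If S-VR has no effect and the rooms differ by 0.1 to 0.5 SD in comfort (assumed), the chance of a significant result rises from 5% to between about 7% and 60% at 34 to 40 per arm. This needs correcting before the comfort result is read as an effect of S-VR alone.

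**What to change.** **If enough participants remain for a balanced swap.** Keep the two arms in separate rooms on any given day, but exchange the rooms on a pre-specified calendar (for example, alternate weeks) that balances the arms across rooms. Record the room for each participant and include it as a covariate in the primary comfort model. The cost is a short amendment and moving the VR equipment and leaflets between rooms. The downside is that staff in both rooms will see both interventions in different weeks. With full balance there is no loss of precision and no change to N.

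**If too few remain.** Do not rely on adjustment for room, because the adjusted estimate would be very imprecise. Instead:
- document how the two rooms and their staffing compare;
- state where T2 is taken and, if it is in the room, make the T2-to-T3 change the main contrast for anxiety, pain and vital signs;
- limit the conclusion on comfort (and on self-efficacy, which has the same timing) to the combined effect of S-VR and room, and report the confounding as a limitation.

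This second route costs nothing in recruitment, but it leaves the effect of S-VR itself on comfort unanswered.

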### Intervention (S-VR plus standard care)

Participants in the intervention arm will receive immersive VR intervention with a VR box (Shinecon 6.0 VR Box Virtual Reality Glasses with headphones). S-VR is a virtual relaxation and distraction therapy administered through a smartphone-based VR device (head-mounted display) mounted to the head of the patient with cancer during chemotherapy. The intervention involves a virtual environment in which 360° videos of natural panoramas with traditional and classical music (non-copyright) are provided. The S-VR device is paired with a smartphone with either an Android (minimum generation 11, Android V.4.4 KitKat) or iOS (V.12, minimum screen size of 5.5 inch and maximum of 6.0-inch, screen resolution of at least 1080×1920 pixels) operating system and the ability to connect to Wi-Fi or the internet and with the YouTube app installed, which they will use to access the 360° videos. The S-VR content comprises original 360° videos approximately 10 min long and produced by the researchers by using video editing software. The video duration was determined on the basis of a previous study by Fabi *et al*^43^ in which this duration was demonstrated to be effective in preventing patient saturation related to content and preventing motion sickness. The 360° videos present panoramic views of Yogyakarta, Indonesia, and Taipei, Taiwan (figure 2). The RA will provide information about the S-VR intervention for approximately 5 min, assist in attaching the S-VR devices to the patient and conduct the intervention for approximately 10 min.

**Figure 2 F2:**
[figure not shown]
360° Videos used in the smartphone-based virtual reality relaxation intervention.

### Control (leaflet plus standard care)

In the control group, participants will be provided with standard care and guided imagery leaflets, which will provide information on the meaning, benefits and methods of completing guided imagery relaxation therapy during chemotherapy. The RA will guide the participants through the practices of the guided imagery relaxation therapy described in the leaflet for ±10 min (figure 3).

**Figure 3 F3:**
[figure not shown]
Guided imagery leaflet.

### Compensation

Compensation will be provided by the researchers to all respondents after the chemotherapy session in the form of a package containing food, beverage and a small towel. These objects are placed in a small bag along with a note of appreciation for participation in this research.

### Safety and side effect management

The intervention of this study is not associated with any significant side effects because it does not involve invasive procedures and is administered for a short period (one chemotherapy cycle). However, we predict that the participants will feel discomfort both while using the VR and during chemotherapy and will record their levels of discomfort on a monitoring sheet. The Virtual Reality Symptom Questionnaire, which was developed by Ames *et al*,^44^ will be administered to patients after the VR intervention in order to assess the possibility of cybersickness, a form of motion sickness caused by exposure to VR. The questionnaire evaluates eight general physical side effects (general discomfort, fatigue, boredom, drowsiness, headache, dizziness, concentration difficulties and nausea) and five visual effects (tired eyes, aching eyes, eyestrain, blurred vision and difficulties focusing). The scoring was modified to a 4-point scale (the original score consisted of a 6-point scale), from 0 to 4 (represented of none, mild, moderate, severe) with 0 indicating the absence of the symptom and 4 indicating its severity. During the study, the researchers will clearly indicate that they can be contacted should the participants have any VR-related problems or complaints or if something unexpected occurs.

### Data analysis

The collected data will be processed using IBM SPSS statistical software V.23 for Windows through editing, coding and data entry processes. The statistician will be blinded to the study outcomes and will conduct analyses on the basis of the labelling of the groups. For the treatment group, the demographic and clinical variables recorded at enrolment will be tabulated. The descriptive statistics will be presented as numbers, means, SDs, medians, minimums and maximums. Homogeneity and normality tests will be conducted before the bivariate analysis test. A homogeneity test for categorical data (age, sex, education level, marital status, occupation, income, the presence of a family member or caregiver during chemotherapy, type of cancer, stage of cancer, duration of cancer diagnosis, chemotherapy cycle and ECOG Scores) will be performed using the χ^2^ test or Fisher’s test, whereas a homogeneity test for numerical data (height and weight) will be performed using Levene’s test if the data are normally distributed and using the Mann-Whitney U test if the data are not normally distributed. Both groups will be considered to be homogeneous if p>0.05. Bivariate analysis will be used to determine the differences in the mean scores for comfort level and symptom management self-efficacy before and after treatment in the intervention and control groups. If the data distribution is normal, we will use a paired t-test and independent t-test. However, if the data distribution is not normal, the non-parametric Wilcoxon and Mann-Whitney U tests will be used if significant differences are identified (p<0.05). For anxiety, pain and vital-sign (blood pressure and pulse rate) outcome measurement analysis, General Linear Model-Repeated Measure (GLM-RM) statistics will be used. The GLM-RM is a statistical test used for the comparative analysis of two unpaired numerical data groups with more than two measurements and is applied when the effect of a treatment or intervention is measured at different time points. If the data are not normally distributed, the repeated Mann-Whitney alternative test with Bonferroni correction will be used. The present study will use statistical method to adjust for potentially confounding effects of the S-VR intervention on the patient’s outcomes. These confounders include age, gender, education, cancer stage, chemotherapy cycle, assistance during chemotherapy and comorbidities. Multivariate model can handle identified confounders and minimise the bias effect of the intervention.^45^ Linear regression analysis will be applied by using the enter method. Adjustment by using this analysis can clarify that how much the confounders in the model distort the intervention and outcome.^46^

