The primary objective of this study is to determine the efficacy of S-VR in increasing comfort in patients with cancer undergoing chemotherapy. The secondary objectives of this study are to assess the effects of S-VR on the symptom management self-efficacy, anxiety, pain and vital signs (pulse and blood pressure) of patients with cancer undergoing chemotherapy. We hypothesise that relative to the control group, the patient group that receives the S-VR intervention will experience greater improvements in their comfort levels.

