T0: baseline data collection (after prechemotherapy assessment and obtaining signed informed consent); T1: before intravenous installation/premedication; T2: before the start of the intervention; T3: immediately after the intervention; T4: after completion of one chemotherapy cycle.

NPRS, Numerical Pain Rating Scale; SE-CSSMS, Self-Efficacy of Cancer Symptom Self-Management Scale; SGCQ, Shortened General Comfort Questionnaire; VAS-A, Visual Analogue Scale for Anxiety.

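### Within-arm and between-arm tests of comfort and self-efficacy stand side by side, and the between-arm contrast is not named as the one that decides efficacy

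*Protocol article*

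**What the plan says.** The Introduction states a comparative hypothesis: "relative to the control group, the patient group that receives the S-VR intervention will experience greater improvements in their comfort levels". The Sample size calculation section uses an effect size of 0.81, two-tailed 5%, 90% power and 1:1 allocation between groups, giving 34 per group and 40 after 15% dropout.

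The Data analysis section gives the purpose of the bivariate analysis of these two outcomes as to "determine the differences in the mean scores for comfort level and symptom management self-efficacy before and after treatment in the intervention and control groups". It continues: "If the data distribution is normal, we will use a paired t-test and independent t-test". For non-normal data it names the Wilcoxon and Mann-Whitney U tests together in the same way. It does not say which test in each pair decides the outcome, or whether the between-arm test compares T4 scores or T0-to-T4 changes. A linear regression on listed confounders follows; the T0 score is not in that list.

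On timing, the Outcomes section and Table 2 place the comfort questionnaire (SGCQ) and the self-efficacy scale (SE-CSSMS) at T0 and T4 only. At T0, "The participants will be evaluated (pretest) by the outcome assessor (research nurse) before they enter the chemotherapy room" (Patient recruitment section). The end point is "T4: after completion of one chemotherapy cycle" (note to Table 2). Between these, the research assistant is to "conduct the intervention for approximately 10 min" in the S-VR arm, and guides control participants through leaflet-based relaxation for a similar time.

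**The concern.** A paired test asks whether the mean changed within one arm. The trial asks whether it changed more in one arm than in the other. Between T0 and T4 a patient enters the chemotherapy room, has intravenous access placed, receives premedication and the infusion, does about 10 minutes of assistant-led relaxation in either arm, and finishes. Any of these may move comfort up or down, and a paired p-value takes in all of them.

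Two parallel paired tests also invite a familiar error: reporting that comfort rose significantly with S-VR but not with the leaflet, as if that were a comparison of the arms. The purpose sentence is worded as before-after and no test is ranked, so nothing in the section prevents such a report. What is at stake is the basis of the claim on the primary outcome.

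**Working it through.** **1. The plan's own figure.** Inputs from the Sample size calculation section: d = 0.81, two-sided α = 0.05, power 0.90, 1:1. For a two-sample t-test with n per group, the noncentrality is d·√(n/2) on 2n − 2 degrees of freedom. At n = 33 power is 0.8998; at n = 34 the noncentrality is 0.81 × √17 = 3.34 and power is 0.908. So 34 per group reproduces, and 34 / (1 − 0.15) = 40 reproduces the inflated figure. The sample size belongs to a between-arm comparison.

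**2. Paired test in the S-VR arm when S-VR has no effect.** Assumptions: both arms share the same natural T0-to-T4 change, expressed as a standardised paired change δ (mean change divided by the SD of change); the arms are independent; 34 patients per arm are analysed; two-sided 5%. The protocol gives no value for δ, so a range is shown. The paired t-test has noncentrality δ·√34 on 33 degrees of freedom, with critical value 2.035. Let a be the probability of significance in either direction and u the probability of a significant improvement. The pattern of a significant improvement with S-VR and no significant change with control then has probability u(1 − a).

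| δ | a: S-VR paired test significant | u(1 − a): S-VR improved, control not |
|---|---|---|
| 0 | 5.0% | 2.4% |
| 0.1 | 8.7% | 7.5% |
| 0.2 | 20.5% | 16.2% |
| 0.3 | 39.7% | 23.9% |
| 0.4 | 62.0% | 23.6% |
| 0.5 | 80.8% | 15.5% |
| 0.6 | 92.4% | 7.0% |
| 0.7 | 97.7% | 2.2% |
| 0.8 | 99.5% | 0.5% |

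Example at δ = 0.3: noncentrality 0.3 × √34 = 1.749, a = u = 0.397 to three places, and 0.397 × 0.603 = 0.239. With 40 per arm the paired test is significant in 5%, 24%, 46%, 87% and 99.9% of trials at δ = 0, 0.2, 0.3, 0.5 and 0.8.

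**3. Between-arm test on the same data.** In 20,000 simulated trials per setting (n = 34 and 40; δ = 0, 0.2, 0.3, 0.5, 0.8), the independent t-test on change was significant in 4.9% to 5.2%. A valid two-sided test wrongly favours S-VR in 2.5% of trials. Change common to both arms cancels in this test and does not in the paired test.

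**The case against.** The strongest reply is that the valid test is already planned. The sentence that names the paired t-test also names the independent t-test, and Mann-Whitney U stands beside Wilcoxon. The hypothesis and the sample size both point to the between-arm contrast; a paired test at a standardised change of 0.81 would reach 90% power with about 19 patients. This stands. A reader might infer from the before-after wording that comfort is tested only within arms, or that natural change over the visit will be counted as an S-VR effect. The document does not support either reading: it plans between-arm tests, and nowhere says that a paired result will be taken as efficacy.

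Two further points stand. The events of the visit occur in both arms, so the T0-to-T4 span is no flaw in the between-arm test. An added questionnaire just before and after the intervention would not rescue a paired test either, because that would still lack a control. And the error rates above belong to a decision rule the protocol does not state: at small or large natural change, the pattern of S-VR only is no more frequent than the 2.5% benchmark.

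The reply that ranking of tests can be left to an analysis plan carries less weight. The article does not merely omit a detail; it states two kinds of test for the primary outcome under a purpose that differs from the hypothesis, and an analysis plan that follows it would inherit the ambiguity.

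**Conclusion.** The point holds as a matter of precedence and wording. The section plans a valid between-arm test and, with equal standing, a within-arm test that does not address the hypothesis, and it gives no rule for choosing between them. If the paired results were used, false claims could be frequent: 5% to 99.5% for the S-VR paired test alone, and about 0.5% to 24% for the pattern of S-VR significant and control not, peaking at a standardised change of 0.3 to 0.4. These figures assume no true arm difference, equal natural change of 0 to 0.8 in both arms, independent arms and 34 analysed per arm. The natural change is an assumption throughout. The planned between-arm test keeps its 5% level, and the sample size is unaffected.

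**What to change.** In the Data analysis section:

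- Make the T0-to-T4 results within each arm descriptive for SGCQ and SE-CSSMS: T0 and T4 means and mean change per arm, without p-values. Drop the paired t and Wilcoxon tests as tests of effect.
- State that efficacy for comfort and for self-efficacy is concluded only from one between-arm comparison, reported with its 95% confidence interval.
- Say what that comparison uses. One suitable choice is the T4 score adjusted for the T0 score (analysis of covariance).
- Reword the purpose sentence to match the hypothesis in the Introduction.

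This costs a few sentences. It needs no further patients, visits or measurements. The only loss is within-arm p-values that do not bear on the hypothesis.
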